#### 4. Assessment at Two Week Follow-Up

We will administer at two week follow-up the NRS [12], FRI [13], and the area specific instruments modified ODI [23] or NDI [24]. These questionnaires will be used to establish the short term efficacy of brief chiropractic care for spinal pain. The FABQ [19] and PCS [22] will also be administered to examine whether cognitive aspects related to the experience of pain influence pain severity, physical function and adverse events.

Also, a global measure of treatment satisfaction [27] and global measure of perceived change [35] will be administered at two week follow-up. The global measure of treatment satisfaction [27] will be used to examine the association between adverse events and treatment satisfaction. It will be measured on a five point categorical scale (very dissatisfied = 0; dissatisfied = 1; no preference = 2; satisfied = 3; very satisfied = 4). The global measure of perceived change [35] will be used to examine the association between adverse events and overall perceived change in the main complaint. It will be measured on an 11 point continuous scale varying from -5 to +5 (-5 = much worse, 0 = unchanged, +5 much better).

Blinding will be assessed at two weeks with a questionnaire [36] that asks the participants if they were in the real treatment group or the sham treatment group. The possible responses are: real treatment group; sham group; or don't know.

### Blinding

Practitioners are unable to be blinded with respect to the participants' treatment group allocation. The statistician and research assistant will remain blind to treatment allocation. We aim to blind participants to the assigned treatment throughout the trial.

### Sample Size

The sample size was based on the number needed to detect a significant difference in the primary outcome (adverse event: yes/no) between groups. We make the assumption that in the usual chiropractic group 45% of patients will experience an adverse event and that the rate in the sham group will be 25%. We believe this is a very conservative estimate given that a) the participants in the Senstad et al. study [3] had 6 treatments and there was a rate of 55% adverse events and b) that for the sham treatment previous studies have shown a mild adverse event rate of 7% [37] using the same de-tuned ultrasound method. Therefore, using a 2-sided test and alpha level of 0.05, recruiting 90 participants in each group (180 total) will provide 80% power to detect a difference this large or larger. G*Power 3.1.3 was used to calculate the sample size [38].

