### Chiropractor Participants

The study interventions will be administered at the clinics of registered chiropractors in Perth, Western Australia. Recruitment of about 12 chiropractors will be by way of open advertisement to the profession using contact details in the public domain or from the online Register of Chiropractors. To be eligible, chiropractors must have had at least two years of clinical experience and regularly use spinal manipulation in the mix of their therapy modalities. Chiropractors who administer the sham intervention must have both ultrasound and Activator^® ^instruments available.

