### Intervention/treatment

Chiropractors will be asked to deliver one of the two study interventions. The study interventions are as follows:

1. Short term usual chiropractic care: a series of two chiropractic treatments to the spine as deemed suitable by a registered chiropractor. Treatments include one or more of the following: spinal manipulation, mobilisation, drop piece, traction, electro- therapies, ultrasound, Activator^®^, soft tissue techniques and other manual techniques offered by the chiropractor. This treatment approach replicates a common pragmatic approach in the field [1].

2. Sham Group: participants will receive two sessions of de-tuned ultrasound and de-tuned Activator^® ^treatment by a chiropractor to the regions where spinal pain is experienced. There is no known treatment benefit from the de-tuned ultrasound machine and it has been established in previous trials as a credible treatment option by patients [17,18]. Chiropractors will be directed to wind the Activator^® ^head force to minimum and then administer the force through a wooden tongue depressor at random locations in the spine near the areas of concern. The dimensions of the depressor are 19 mm wide and 150 mm long, although on average only 600 mm of the length will be in contact with the skin. This means a surface area of 1140 mm^2^. We measured the force this will provide to the skin using a force transducer. The mean of 5 measured attempts was a very low 3.7 kPa. To increase the perceived "hands on" credibility, the chiropractor will be trained to gently place one hand on an area adjacent to the participant's spine while delivering the ultrasound and Activator^® ^therapies. The four chiropractors recruited to deliver the sham treatment will be asked to administer the sham interventions as they normally use Activator^® ^tools and ultrasound and with the same enthusiasm they would use for all other therapies.

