#### Analysis of Adverse Events

The primary outcome (adverse event; yes/no) will be compared between groups. The severity and frequency of adverse events will be reported descriptively. Logistic regression will be used to examine associations between adverse events and several factors. Factors which have been significantly associated with adverse events in previous studies will be selected for this study. These factors comprise treatment satisfaction [4], manipulation/mobilisation [4], global improvement [4], GP visit in last six months [6], duration of neck/back pain [6], medication use [29], gender [29], and age [29]. The relative risk [39] will be calculated using a two by two contingency table and 95% confidence intervals. The number needed to harm [40] will be calculated with 95% confidence intervals to identify the number of individuals needed to be exposed to a risk factor (chiropractic treatment) over a specific period to cause harm (adverse outcome) in one patient that would not otherwise have been harmed. Data will be assessed by using per protocol analysis. In addition, an intention to treat analysis will be undertaken by using sequential regression multiple imputation [41].

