## Discussion

To our knowledge, this is the first study to use a sham-controlled arm to examine the rate of adverse events during chiropractic care. It also appears to be the first controlled study to investigate how often adverse events occur during chiropractic care for spinal pain, as the only other controlled chiropractic study examined adverse events for chiropractic treatment of neck pain. The findings of this study will build on the limited number of previous studies conducted to examine adverse events during chiropractic care and contribute towards a more robust understanding of the safety profile of chiropractic care. In particular, the inclusion of a sham arm will enable us to better discern the rate of actual adverse events by comparing the frequency of adverse events that occurred in the usual chiropractic care group to those in the sham controlled group. This study will also provide additional evidence about the efficacy of short term usual chiropractic care for spinal pain.

There are three main limitations associated with the conduct of this study. First, we will only be able to provide two treatment sessions to each participant due to funding constraints. Consequently, in all likelihood our study will only capture the most common adverse events of chiropractic care. Second, the internal validity of this trial would have been enhanced by having the same chiropractors provide both interventions. However, we decided to use a different group of chiropractors to provide each intervention as we anticipated difficulty in recruiting sufficient chiropractors with access to both ultrasound and Activator^® ^instruments, both of which are required to administer the sham intervention. Third, the extent to which we can accurately determine the relative risk of usual chiropractic care depends on how well we are able to maintain blinding to treatment allocation. We acknowledge that it may be difficult to blind the participants with spinal pain to the assigned treatment throughout the trial and accordingly will examine blinding through administering a questionnaire. However, our findings about the success of blinding should be viewed cautiously as the questionnaire we will use to assess blinding has not been formally validated.

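### The 80% power and the 95% intervals treat 180 participants as independent although chiropractor is nested in arm; both are too favourable if outcomes cluster by chiropractor

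*Protocol article*

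**What the plan says.** The structure has to be assembled from three places in the protocol article.

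- Chiropractor Participants: "Recruitment of about 12 chiropractors will be by way of open advertisement to the profession".
- Intervention/treatment: "The four chiropractors recruited to deliver the sham treatment will be asked to administer the sham interventions". The same section leaves usual care to each chiropractor's judgement.
- Discussion: "we decided to use a different group of chiropractors to provide each intervention as we anticipated difficulty in recruiting sufficient chiropractors". The section names this as a limit on internal validity.

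Participants are randomised individually, 1:1 (Treatment allocation). Under Sample Size, the calculation assumes adverse event rates of 45% with usual care and 25% with sham, "using a 2-sided test and alpha level of 0.05", and concludes that "recruiting 90 participants in each group (180 total) will provide 80% power to detect a difference this large or larger". No ICC or design effect appears.

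Under Analysis of Adverse Events: "The primary outcome (adverse event; yes/no) will be compared between groups", and "The relative risk [39] will be calculated using a two by two contingency table and 95% confidence intervals". A number needed to harm with a 95% interval follows. The factors listed for the logistic regression do not include the chiropractor. Under Analysis of Secondary Outcomes, efficacy is compared by repeated measures ANOVA and a chi-squared test, also without a provider term.

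**The concern.** No chiropractor treats in both arms, so variation between chiropractors does not cancel in the arm comparison. If chiropractors differ in how often their patients have, or report, an adverse event, that variation enters the difference between arms in full. It is averaged over only four people on the sham side and about eight on the other. A calculation that counts 180 independent participants leaves it out.

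At stake is the primary safety comparison. Intervals around the relative risk and number needed to harm would be narrower than the data justify, a false positive would be more likely than 5%, and the chance of detecting the assumed difference with a valid test would be below 80%.

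**Working it through.** **Inputs from the article.** Rates 0.45 and 0.25, two-sided alpha 0.05, 90 per arm, four sham chiropractors, about 12 in total.

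**Inferred.** Usual-care chiropractors: about 12 − 4 = about 8. Average participants per chiropractor: 90/4 = 22.5 (sham) and 90/8 = 11.25 (usual care).

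**Assumed.** ICC of 0.01, 0.02 or 0.05, because the article gives none.

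**Step 1: reproduce the plan's figure.** With independent participants:

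- SE under the null = √(0.35 × 0.65 × 2/90) = 0.0711
- SE under the alternative = √((0.45 × 0.55 + 0.25 × 0.75)/90) = 0.0695
- Power = Φ((0.20 − 1.96 × 0.0711)/0.0695) = Φ(0.872) = 80.8%

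The same formula needs 89 per arm for 80% power. The stated 90 and 80% are therefore correct as an independent-participant calculation.

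**Step 2: add clustering.** The design effect in each arm is DE = 1 + (m − 1) × ICC, with m the average number per chiropractor. Each arm's variance is multiplied by its own DE. At ICC 0.02:

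- DE usual care = 1 + 10.25 × 0.02 = 1.205; DE sham = 1 + 21.5 × 0.02 = 1.43
- SE null = √(0.2275 × (1.205 + 1.43)/90) = 0.0816
- SE alternative = √((0.2475 × 1.205 + 0.1875 × 1.43)/90) = 0.0793
- Power = Φ((0.20 − 1.96 × 0.0816)/0.0793) = Φ(0.505) = 69.3%

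**Step 3: the range, with the same ICC in both arms.** Type I error (true rate 35% in both arms) and relative-risk coverage (45% vs 25%) come from 200,000 beta-binomial simulations of an unadjusted analysis with eight and four chiropractors.

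| ICC | DE usual care / sham | Power, normal | Power, noncentral t, 10 df | Type I error | Coverage of nominal 95% RR interval | Correct / unadjusted width of risk-difference interval |
|---|---|---|---|---|---|---|
| 0 | 1.00 / 1.00 | 80.8% | 73.7% | 5.1% | 95.2% | 1.00 |
| 0.01 | 1.10 / 1.22 | 74.9% | 67.7% | 7.0% | 93.1% | 1.07 |
| 0.02 | 1.21 / 1.43 | 69.3% | 62.4% | 9.0% | 91.0% | 1.14 |
| 0.05 | 1.51 / 2.08 | 55.8% | 50.1% | 14.8% | 84.8% | 1.33 |

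The 10 df are 12 chiropractors minus two arms. The t column must be read against its own first row: the small number of clusters costs about seven points even at ICC 0, so only the fall from 73.7% is due to clustering.

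**Step 4: sensitivity.**

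- Only usual care clustered (sham ICC 0): power, normal reference, 78.8% / 76.8% / 71.0% at usual-care ICC 0.01 / 0.02 / 0.05; type I error about 6% / 6% / 8%.
- Twelve usual-care chiropractors plus four sham: power 75.6% / 70.6% / 58.1%.
- More participants with the same 12 chiropractors: 80% power (normal reference) needs 105 / 129 / 452 per arm.

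**The case against.** **The size rests on an ICC that the article does not give, and equal ICCs are a choice.** This stands. Sham is closely scripted (de-tuned ultrasound, minimum instrument force through a tongue depressor, a trained hand placement), while usual care is discretionary. Sham chiropractors can still differ in manner, but an ICC near zero in that arm is possible, and the loss is then much smaller. Both patterns should be shown.

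**The article already concedes the provider problem.** In part. The Discussion accepts that separate providers weaken internal validity. It does not carry this through to the power or the intervals, which is the point made here.

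**Analysis detail belongs in a statistical analysis plan.** This would answer a silence. Here the article itself states the power and specifies the two by two relative risk with its interval.

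**No primary test is named.** Correct. The article says only that the outcome is compared between groups; chi-squared is named for the minimum acceptable outcome. The type I error figures therefore describe the natural unadjusted test, not a specified one. The relative-risk interval is specified.

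**Stronger readings that the article does not support.** A reader might infer that the sample size is miscalculated; it reproduces under its own assumption. A reader might take 56% or 50% as the trial's actual power; these are values at an assumed ICC of 0.05, and part of the shortfall in the t figures comes from the reference distribution. A reader might also conclude that the sham chiropractors should treat in both arms. That is a design trade-off: unblinded practitioners giving both interventions could weaken participant blinding, which the Discussion already calls difficult.

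**Conclusion.** The point holds in conditional form. Chiropractor is fully nested in arm, with only four sham providers, while the 80% power and the relative-risk and number-needed-to-harm intervals assume independence. For any ICC above zero the power is overstated and the intervals are too narrow.

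The amount is uncertain. At ICCs of 0.01 to 0.05, power with a normal reference lies between about 75% and 56% if both arms cluster equally, and between about 79% and 71% if only usual care does. The count of eight usual-care chiropractors is a subtraction from an approximate total, but taking 12 instead changes little.

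**What to change.** 1. Report the primary comparison (relative risk, risk difference, number needed to harm) and the efficacy comparisons with chiropractor as the cluster and a small-sample correction, for example a cluster-level analysis or a random intercept with about 10 df. Say that four sham clusters make any such estimate imprecise.
2. Replace the flat 80% with power over a range of ICCs for the planned number of chiropractors in each arm. Include a case in which the sham ICC is lower than the usual-care ICC, and name the reference distribution used.
3. State that clustering corrects precision only. It cannot separate a provider effect from a treatment effect, because no chiropractor delivers both interventions.

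The cost is a change of wording, wider intervals and a less favourable stated power. No change to treatment delivery is needed.

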#### Statistical Methods

Data will be entered and analysed in SPSS Version 17. Data will be checked for implausibility's by using a frequency analysis of each variable. In addition, a second check of half the data entered will be made in detail for errors. Descriptive statistics will be derived for the participants' and chiropractors' demographic characteristics, and the types of treatments used. The measurements taken at baseline for the participants will be compared to establish whether the groups are similar.

#### Analysis of Adverse Events

The primary outcome (adverse event; yes/no) will be compared between groups. The severity and frequency of adverse events will be reported descriptively. Logistic regression will be used to examine associations between adverse events and several factors. Factors which have been significantly associated with adverse events in previous studies will be selected for this study. These factors comprise treatment satisfaction [4], manipulation/mobilisation [4], global improvement [4], GP visit in last six months [6], duration of neck/back pain [6], medication use [29], gender [29], and age [29]. The relative risk [39] will be calculated using a two by two contingency table and 95% confidence intervals. The number needed to harm [40] will be calculated with 95% confidence intervals to identify the number of individuals needed to be exposed to a risk factor (chiropractic treatment) over a specific period to cause harm (adverse outcome) in one patient that would not otherwise have been harmed. Data will be assessed by using per protocol analysis. In addition, an intention to treat analysis will be undertaken by using sequential regression multiple imputation [41].

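### The factor list for the adverse-event logistic regression omits randomised arm and no analysis population is stated; if both arms are pooled, its odds ratios mix background reporting with events linked to chiropractic care

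*Protocol article*

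**What the plan says.** All of the text at issue is in the protocol article, Analysis of Adverse Events.

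- The arm comparison comes first: "The primary outcome (adverse event; yes/no) will be compared between groups".
- The regression follows: "Logistic regression will be used to examine associations between adverse events and several factors".
- The factors are chosen by a rule: "Factors which have been significantly associated with adverse events in previous studies will be selected for this study".
- They are then listed: "These factors comprise treatment satisfaction [4], manipulation/mobilisation [4], global improvement [4], GP visit in last six months [6"], and "duration of neck/back pain [6], medication use [29], gender [29], and age [29"]. That makes eight. Neither randomised arm nor a factor-by-arm term is included.
- The text then returns to the two-group comparison: "The relative risk [39] will be calculated using a two by two contingency table and 95% confidence intervals", followed by the number needed to harm.

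The section does not say whether the regression uses both arms or usual care only.

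Other sections bear on the point. Materials and methods explains that the sham arm is there to distinguish events of active care from those of sham treatment or natural history. The Discussion says the sham arm will help to "better discern the rate of actual adverse events by comparing the frequency of adverse events that occurred in the usual chiropractic care group" with that in the sham group. Intervention/treatment places manipulation and mobilisation among the usual-care options and not in the sham. The section on chiropractor demographics and usual-care characteristics provides a treatment checklist for usual-care appointments only.

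**The concern.** The trial rests on the idea that a reported event is not evidence of harm until it is set against sham. A pooled regression without arm does not use that comparison. A factor that raises symptom reporting equally in both arms would look like a risk factor. A factor that raises risk only under real treatment would be diluted by sham events.

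The selection rule explains how arm came to be left out. By the Discussion's own account, this is the first study to use a sham arm to examine adverse events during chiropractic care. A list drawn from earlier studies would therefore not be expected to contain arm.

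Manipulation/mobilisation raises a further problem in a pooled model. Every sham patient is negative on it, so its coefficient would carry some or all of the arm effect and could be read as an effect of technique.

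What is at stake is the interpretation of the only planned analysis of which patients have events. The estimate of how many more events occur under usual care is not at stake.

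**Working it through.** **Inputs.** Sample Size assumes that in usual care "45% of patients will experience an adverse event and that the rate in the sham group will be 25" per cent, with 90 per group, two-sided alpha 0.05 and 80% power. Treatment allocation is 1:1.

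**The plan's own figure.** n per arm = [1.96·√(2·0.35·0.65) + 0.8416·√(0.45·0.55 + 0.25·0.75)]² / 0.20² = (1.322 + 0.555)² / 0.04 ≈ 88.1, so 89. Power at 90 per arm is 80.8%. The stated 90 and 80% are reproduced.

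**Make-up of the events.**
- Usual care 90 × 0.45 = 40.5; sham 90 × 0.25 = 22.5; total 63.
- Sham share of a pooled model: 22.5/63 = 36%.
- Excess over sham: 40.5 − 22.5 = 18, or 18/63 = 29% of all events.
- In a usual-care-only model, 25/45 = 56% of events would be expected under sham anyway.

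**Assumption for the next steps.** The factor is binary, present in half of each arm (45 per cell), and unrelated to arm. The article gives no prevalence.

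**Example 1, factor acts only under real care.** Usual-care risk is 35% without and 55% with the factor; sham is 25% at both levels.
- OR in usual care: (0.55/0.45)/(0.35/0.65) = 2.27.
- Pooled risks: (35 + 25)/2 = 30% and (55 + 25)/2 = 40%. Pooled OR: (0.40/0.60)/(0.30/0.70) = 1.56.
- Wald power is about 47% within usual care and 29% pooled (simulation: 48.5% and 28.7%).

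**Example 2, factor acts on background reporting only.** It adds 20 points in both arms: usual care 35% and 55%, sham 15% and 35%. The excess over sham is 20 points at both levels.
- Pooled OR: (0.45/0.55)/(0.25/0.75) = 2.45, significant in about 79% of trials (simulation 79.9%).

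**Different mechanisms, similar pooled results.** Holding the arm means at 45% and 25%, an OR of 3 in usual care only gives a pooled OR of 1.80. An OR of 3 in sham only gives 1.55. An OR of 2 in both arms gives 1.94.

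**Manipulation/mobilisation with no effect of its own.** Let a share m of usual-care patients receive it (m is assumed). Risk in recipients is 45%. Risk in all others is [90(1 − m)·0.45 + 22.5] / [90(1 − m) + 90].
- m = 0.5: 42.75/135 = 31.7%, OR 1.77.
- m = 0.8: 28.3%, OR 2.07.
- m = 1: 25%, OR 2.45, which is the arm odds ratio itself.

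**What an interaction term can deliver.**
- Example 1: the ratio of ORs is 2.27 and its log is 0.820. Variance = 1/(45·0.35·0.65) + 1/(45·0.55·0.45) + 2/(45·0.25·0.75) = 0.0977 + 0.0898 + 0.2370 = 0.4245, so SE 0.652. z = 1.26 and power is about 24%.
- If 20% or 80% have the factor (cells of 18 and 72) at the same risks, the variance is about 0.656 or 0.671 and power about 17%. The pooled OR of 1.56 does not change.
- A ratio of ORs of 3 has about 39% power; 80% power needs a ratio of about 6.
- Example 2: the sham OR is (0.35/0.65)/(0.15/0.85) = 3.05, so the ratio of ORs is 2.27/3.05 = 0.74 although the excess risk is constant. The arm contrast must therefore be shown as a risk difference too. It is 20 and 20 points here, against 10 and 30 points in Example 1.

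**The case against.** The strongest reply is that pooling is nowhere stated. Some text points the other way: treatment types are recorded only at usual-care appointments, sham patients cannot receive manipulation or mobilisation, and several listed factors come from studies of patients all treated by chiropractors. In a usual-care-only model, leaving out arm is correct and the dilution in Example 1 disappears. This stands as a limit on the claim. It does not settle the matter, because no restriction is written and the neighbouring sentences all concern the two-group comparison. A usual-care-only model would also still mix background with attributable events.

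Second, the article promises only associations, and neither aim mentions predictors of harm. That is right. A reader might infer that the plan claims to identify who is at risk from chiropractic care, or that it repeats the fault of the uncontrolled studies. The documents support neither. The Background faults those studies for possibly overestimating event frequency, and frequency is compared with sham here. The Discussion sentence on actual adverse events refers to that group comparison, not to the regression.

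Third, an interaction term would have little power and its meaning depends on the scale. Both parts are correct, as Examples 1 and 2 show. They limit how the results may be presented, but they do not justify leaving arm out of a pooled model.

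**Conclusion.** The point holds, conditionally and for a secondary analysis. The stated list omits arm and no population is given. On the natural, pooled reading, 36% of the expected events are sham events, and the factor odds ratios cannot distinguish background reporting from events linked to treatment. Manipulation/mobilisation would show a crude odds ratio of about 1.77 to 2.45 from the arm effect alone.

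The 36% follows from the planning rates only. The worked odds ratios assume the risks shown; the power figures also assume a factor prevalence (half, with 20% and 80% tried for the interaction). The proxy range assumes that 50% to 100% of usual-care patients are manipulated or mobilised.

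It would go too far to conclude that the trial's harm estimate is compromised. The between-group comparison, relative risk, number needed to harm and sample size are unaffected. The text should be corrected, but the design need not change.

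**What to change.** 1. State the analysis population of the regression.
2. If both arms are pooled, include randomised arm in every model.
3. For each baseline factor (GP visit, pain duration, medication use, gender, age), one at a time because about 63 events will not carry all interactions together, report the factor's effect in each arm. Add the arm contrast at each factor level as a risk difference and an odds ratio, and the interaction with its 95% interval. Label all of this exploratory. Arm as a main effect alone is not enough: in Example 2 the factor would still have an odds ratio of 2.27 to 3.05 within the arms.
4. Examine manipulation/mobilisation within usual care only.
5. Do not present pooled odds ratios unadjusted for arm as risk factors for harm from chiropractic care.

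The cost is a few sentences and a few lines of code, with no change to sample size or data collection. The downside is wide interaction intervals (about 24% power in Example 1 with a 50:50 factor), so the results can only be descriptive, and an interaction that is not significant must not be read as showing equal harm across patients.

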#### 2. Baseline Assessment

The following questionnaires will be administered at baseline: demographic questionnaire; NRS [12]; FRI [13]; Fear-Avoidance Behaviour Questionnaire (FABQ) [19]; SF-36 [20]; STarT Back Musculoskeletal Screening Tool [21]; and the Pain Catstrophising Scale (PCS) [22]. Also, the primary area of concern for each participant will be identified and one of the following questionnaires specific to that area will be administered: the modified Oswestry Disability Index (ODI) [23]; or Neck Disability Index (NDI)[24].

Descriptive statistics from the baseline measures including the SF-36, STarT Back Musculoskeletal Screening Tool, and demographic questionnaire will be examined to determine if clinically important differences are evident between the usual chiropractic group and sham group at baseline. The SF-36 is a well validated and extensively used measure of general health status [25]. The STarT Back Musculoskeletal Screening Tool is brief validated instrument that has been developed to identify people with chronic pain who are more likely to experience persistent symptoms [21]. The demographic questionnaire enquires about age, sex, race/ethnicity, education, household income, marital status, employment status, smoking, and alcohol and legal drug consumption. These items were derived from classifications used by the Australian Bureau of Statistics [26].

A baseline symptom checklist will be administered to examine whether the adverse events that participants reported after each chiropractic treatment were actually an adverse event or the persistence of a presenting complaint. This will be achieved through comparing data from the symptom checklist taken at baseline to data from the adverse event checklist collected after each chiropractic treatment.

The NRS contains an 11-point scale varying from 0 (no pain) to 10 (worst pain imaginable) [12]. It is a valid, reliable and responsive measure of pain intensity [27]. Participants will be asked to use the scale to rate: their worst level of pain in the last two days; average pain level in the last two days; best pain level in the last two days; and current pain.

The FRI contains 10 questions which enquire about the impact of neck and back pain on physical function. It was designed to assess conditions where more than one area of the spine is involved and is valid, reliable and responsive [13].

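### The only stated between-arm estimate for adverse event yes/no is an unadjusted two-by-two relative risk; a prespecified baseline-adjusted one would cost little, gain modest precision and limit chance imbalance

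*Protocol article*

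**What the plan says.** Under Analysis of Adverse Events the protocol article says: "The primary outcome (adverse event; yes/no) will be compared between groups". It names no test. The effect measure is explicit: "The relative risk [39] will be calculated using a two by two contingency table and 95% confidence intervals". A number needed to harm with a 95% interval follows.

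The same section plans a logistic regression of adverse events on several factors: "Factors which have been significantly associated with adverse events in previous studies will be selected for this study". Eight are listed, and treatment arm is not among them. Five describe the participant before treatment: GP visit in the last six months, duration of pain, medication use, gender and age. The other three are treatment satisfaction, manipulation/mobilisation and global improvement.

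Under Treatment allocation, baseline measures are taken before allocation, and the sequence uses permuted blocks with no stratification factor stated. Under Statistical Methods, "The measurements taken at baseline for the participants will be compared to establish whether the groups are similar"; no adjustment is tied to the result. Under 2. Baseline Assessment, a symptom checklist is collected so that new events can be told from persisting complaints, by "comparing data from the symptom checklist taken at baseline to data from the adverse event checklist collected after each chiropractic treatment".

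**The concern.** The article fixes a crude relative risk as the primary estimate while holding baseline information that it says bears on the outcome. Two things are at stake.

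- **Precision.** If baseline variables predict who reports an event, a model that uses them gives a narrower interval from the same 180 participants.
- **Chance imbalance.** With 90 per arm and no stated stratification, the arms can differ by chance on a prognostic factor. A crude relative risk and number needed to harm carry that difference. Comparing the arms at baseline would reveal it but would change no estimate. Choosing an adjustment afterwards would be open to the charge of selection.

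**Working it through.** **Inputs.** From Sample Size: the assumption that "in the usual chiropractic group 45% of patients will experience an adverse event", 25% in the sham group, 90 per arm, and a sample size derived "using a 2-sided test and alpha level of 0.05". Not given anywhere: the correlation (rho) between baseline variables and the outcome within arm. It is an assumption here and is shown as a range.

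**1. The plan's own figure.** Pooled rate 0.35.
- Null SE = sqrt(2 × 0.35 × 0.65 / 90) = 0.0711.
- Alternative SE = sqrt(0.45 × 0.55 / 90 + 0.25 × 0.75 / 90) = 0.0695.
- Power = Φ[(0.20 − 1.96 × 0.0711) / 0.0695] = Φ(0.872) = 80.8%.
- The same formula solved for 80% power gives 89 per arm.

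The stated 90 per group therefore reproduces as an unadjusted comparison. At the planning rates the relative risk is 1.80 (95% CI 1.18 to 2.75). The risk difference is 20 points with half-width 1.96 × 0.0695 = 13.6 points. The number needed to harm is 5 (3.0 to 15.7).

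**2. Effect of adjustment.** Multiply both variances by (1 − rho²) and recompute.

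| Assumed rho | Power | Gain (points) | Half-width of risk difference (points) |
|---|---|---|---|
| 0 | 80.8% | 0 | 13.6 |
| 0.15 | 81.7% | 0.9 | 13.5 |
| 0.20 | 82.4% | 1.6 | 13.4 |
| 0.27 | 83.7% | 2.9 | 13.1 |
| 0.35 | 85.7% | 4.8 | 12.8 |
| 0.50 | 90.6% | 9.8 | 11.8 |

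**3. Which rho is plausible?** Take a baseline factor with an assumed prevalence of 50%. Solve for the event risks in those without and with the factor that average to the arm's rate at a given odds ratio. Then rho = 0.5 × (risk with − risk without) / sqrt(p(1 − p)).
- Odds ratio 2: sham risks 18.6% and 31.4%, rho 0.15; chiropractic risks 36.5% and 53.5%, rho 0.17.
- Odds ratio 3: sham risks 15.1% and 34.9%, rho 0.23; chiropractic risks 31.7% and 58.3%, rho 0.27.
- Rho of 0.35 needs an odds ratio of about 5, and 0.5 needs about 13.

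**4. Check by simulation.** Logistic regression with one standard normal baseline covariate, 90 per arm, 6,000 replicates. Unadjusted against adjusted power:
- 82.3% and 81.7% when the covariate is not prognostic;
- 81.8% and 83.1% at R² of about 0.05 (rho about 0.22);
- 81.7% and 85.3% at R² of about 0.10 (rho about 0.32).

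Type I error was 4.5% to 5.4% across both analyses. A second simulation (3,000 trials per setting) used standardised logistic regression with five covariates. It gave 81.4% unadjusted and 80.9% adjusted when none was prognostic, so needless adjustment costs about half a point.

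**5. Chance imbalance.** For a factor of assumed 50% prevalence, the SD of the between-arm difference is sqrt(2 × 0.25 / 90) = 7.5 points. The probability of a gap above 10 points is 2 × [1 − Φ(0.10 / 0.0745)] = 18%; above 15 points it is 4.4%. At odds ratio 3 the risk gap is 34.9 − 15.1 = 19.8 points (sham) or 58.3 − 31.7 = 26.6 points (chiropractic). A 10-point imbalance would then move the crude risk difference by about 0.10 × 19.8 = 2.0 to 0.10 × 26.6 = 2.7 points.

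**The case against.** The strongest reply is that nothing is wrong. A two-by-two comparison is valid under randomisation, holds its type I error, and is what the sample size was built on. Chance imbalance is random error that the 95% interval already covers. All of that stands. A reader might infer that the crude analysis is biased or that the stated 80% power is lost; the recalculation supports neither.

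Second, this is a condensed article. A fuller plan could add arm to the logistic regression, and the primary test is unnamed. That also stands. The point is limited to what the article does fix: the only stated effect estimate is the crude relative risk.

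Third, a reader might treat the symptom checklist as a baseline version of the outcome and expect a large gain from it. The documents do not support that. The checklist is meant to screen persisting complaints out of the outcome. What remains between baseline symptoms and a new event may be weak, absent or negative, since a person with more symptoms at the start has fewer left to develop.

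Fourth, the article's list of associated factors was drawn up for a separate association analysis. Three of its eight entries arise after randomisation, and baseline pain on the NRS is not on it. The list is evidence that some baseline factors matter. It is not a ready-made adjustment set.

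Finally, the baseline comparison of the groups is ordinary description. The article does not offer it as a remedy for imbalance, so it should not be faulted as a failed one.

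**Conclusion.** The concern holds as a suggested improvement. The stated primary estimate leaves out baseline information that the trial has or needs for its own regression, and neither the stated design nor the stated analysis limits the effect of chance imbalance on it.

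The likely size is small: about 1 to 3 power points, and an interval about 1% to 4% narrower, for rho of 0.15 to 0.27. That range rests on an assumed single factor of 50% prevalence with an odds ratio of 2 to 3; several factors together could do somewhat better. Gains of 5 to 10 points need rho of 0.35 to 0.5. A reader might take those as the expected benefit, but a report that factors were significantly associated in earlier studies says nothing about strength of that order. The case rests on the low cost and the protection against imbalance as much as on power.

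**What to change.** In Analysis of Adverse Events, prespecify the main between-arm estimate as follows.

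- Fit a logistic model of adverse event (yes/no) on randomised arm plus a short fixed list of baseline variables: age, gender, duration of pain, baseline medication use and one named baseline NRS rating (four are collected). Baseline symptom count is optional and should not be presented as the main source of gain.
- Standardise the predicted risks over the whole trial sample. Report the marginal relative risk, and the marginal risk difference from which the number needed to harm follows, with robust 95% intervals.
- State that treatment satisfaction, manipulation/mobilisation and global improvement are excluded from this model because they arise after randomisation. They may stay in the separate association analysis.
- Keep the crude two-by-two relative risk as a supporting analysis.
- Fix the list before unblinding, and do not let the baseline comparison decide it.

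The cost is a wording change and a little more programming. No extra participants are needed. The article does not name the form that records duration of pain, but its own regression already requires it; it should be confirmed as recorded before allocation. About 90 × 0.45 + 90 × 0.25 = 63 events are expected, or 63 / 6 = 10.5 per coefficient for arm plus five covariates (63 / 7 = 9 with symptom count), if each enters as a single term.
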